# INTRODUCTION

###### The purpose of this document is to describe the statistical methods, data derivations and data summaries to be employed in the study entitled “Perioperative ketorolac in cancer patients with inflammation - Rationale, feasibility and methodology of a prospective randomized trial”.

The preparation of this statistical analysis plan (SAP) has been based on International Conference on Harmonisation (ICH) E3 and E9 Guidelines and in reference to Protocol 2021-003-774-76 / KBCt, November 25th, 2012, version 2.5.

.

# ABBREVIATIONS A COMPLETER

The following abbreviations will be used within this SAP.

DFS Disease-Free Survival

DSMB Data Safety Monitoring Board

FAS Full Analysis Set

LFS Locoregional-Free Survival

MFS Metastasis-Free Survival

OS Overall Survival

PP Per-Protocol Analysis Set

RFS Recurrence-Free Survival

SAE Serious Adverse Event

SAP Statistical Analysis Plan

SAS® SAS® Software

# STUDY OBJECTIVES

### Primary Objectives

- The primary objective of this study is to evaluate the effect of perioperative ketorolac on disease-free survival (DFS) after at least 2 years of follow-up in high risk breast cancer patients.

### 3.2 Secondary Objectives

The secondary objectives are as follows:

- To examine the effect of perioperative ketorolac on LFS at 2 and 5 years in high risk breast cancer patients.
- To examine the effect of perioperative ketorolac on Metastasis-Free Survival (MFS).
- To examine the effect of perioperative ketorolac on Overall Survival (OS)
- To examine the effect of perioperative ketorolac on post-operative pain and peri- and post-operative blood loss.
- To determine the safety profile of perioperative ketorolac based on serious adverse events (SAEs)

# STUDY DETAILS

### 4.1 Overall Study Design

This is a national, multicenter, prospective, double-blind, placebo-controlled, randomized phase III trial of peri-operative ketorolac in high risk breast cancer patients.

Patients providing written informed consent will be assessed at a screening visit to determine their eligibility for the trial. Those eligible will be asked to attend the trial center at baseline, corresponding to the day of surgery. Each patient will be assigned to one group (ketorolac or placebo), and 1 dose of ketorolac (30 mg) or placebo, identically presented, will be attributed to the patient for ulterior administration. A closed envelope joined to the medications will permit potential immediate unblinding for emergency cases. In both groups, the administration of the study drug (ketorolac or placebo) will be done during the induction of anesthesia (pre-incision).

### 4.2 Study Events Flow Chart

Table A provides a detailed description of the schedule of events.

Table A: Schedule of events

|  | **Screening** | **Treatment** | **Hospital discharge** | **Follow-up at 1, 2, 5 years** |
| --- | --- | --- | --- | --- |
|  | **D-21 to D0** | **D0** | **D8** | **1, 2, 5 years** |
| Written consent | X |  |  |  |
| Inclusion/exclusion criteria | X | X |  |  |
| Randomization |  |  |  |  |
| Baseline data | X |  |  |  |
| Medications | X |  | X | X |
| Histology |  |  | X | X |
| Hospital discharge |  |  | X |  |
| Follow-up at 1 year |  |  |  | X |
| Follow-up at 2 years |  |  |  | X |
| Follow-up at 5 years |  |  |  | X |
| Chemotherapy |  |  | X | X |
| Radiotherapy |  |  | X | X |
| Chronic pain |  |  |  | X |
| Locoregional recurrence assessment |  |  |  | X |
| Distant metastases |  |  |  | X |
| Tumor biomarkers |  |  |  | X |
| Cardiovascular assessment |  | X | X | X |
| Gastro-intestinal assessment |  | X | X |  |
| Blood loss |  | X | X |  |
| Serious Adverse Event |  | X | X |  |
| Death information | X | X | X | X |
| Unblinding |  | X |  |  |
| Screening Log | X |  |  |  |

### 4.3 Interim Analysis

No interim analysis will be performed for this study.

### 4.4 Data Safety Monitoring Board

No Data Safety Monitoring Board (DSMB) meeting will be performed for this study.

### 4.5 Sample Size Determination

Sample size estimation is presented in the protocol. Patient numbers were based on the following assumptions:

Based on a reduction of recurrence of 33%, with a type I error of 5% and a power of 80%, the number of patients eligible is of 200 (Log Rank test), randomized in a 1:1 ratio between ketorolac and placebo.

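### Section 4.5 states 80% power for 200 patients without condition, but its listed assumptions support this only if the event risk is very high

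*SAP*

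**What the plan says.** SAP section 4.5 refers to the protocol for the estimation and then lists what the patient number rests on. It begins "Based on a reduction of recurrence of 33" percent, continues "with a type I error of 5% and a power of 80%, the number of patients eligible is of 200 (Log Rank test"), and adds that patients are "randomized in a 1:1 ratio between ketorolac and placebo". The section does not say whether the 33% is a reduction in hazard or in the proportion of patients recurring. It gives no sidedness, control risk or number of events.

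The Primary Objectives define the target as "disease-free survival (DFS) after at least 2 years of follow-up". Section 10.9.1 makes the log-rank comparison of DFS the primary analysis. Section 4.3 plans no interim analysis, and the SAP ties the final analysis to no event count.

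**The concern.** For a given effect, the power of a log-rank test is set by the number of events. Patients matter only through the events they supply. Section 4.5 names the log-rank test but goes directly from effect, error rate and power to a patient count. The count it reaches, 200, is close to the number of events that an HR of 0.67 would need.

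If the event risk by the analysis is moderate, the true power for the planned effect is well below 80%. A non-significant DFS result would then be read as evidence against a 33% reduction, although the trial had only a limited chance of detecting one.

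**Working it through.** **Inputs from the SAP.** Section 4.5: 33% reduction, 5% type I error, 80% power, log-rank test, 1:1, 200 patients.

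**Assumptions.** Two-sided test: z = 1.960 + 0.8416 = 2.8016, z² = 7.849. The control risk p0 (cumulative probability of a DFS event by the analysis) is not in the SAP and is shown as a range. With 100 patients per arm, events D = 100 × (p0 + p1), where p1 is the ketorolac risk. Power = Φ(√D × |ln HR| / 2 − 1.960).

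**Step 1: can 200 be reproduced?** With HR 0.67:
- Schoenfeld: 4 × 7.849 / (ln 0.67)² = 31.396 / 0.16038 = 195.8, so 196 events.
- Freedman: 7.849 × (1.67 / 0.33)² = 201.01, so 202 events.

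With HR 2/3 the results are 191 and 197. One-sided tests need 151 to 159 events. So 200 is close to the two-sided event count, but the SAP gives it as patients. For 200 patients to supply 196 events, 196/200 = 98% must have an event. The Freedman count of 202 is out of reach even if all of them do.

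**Step 2: hazard reading.** HR 0.67 gives p1 = 1 − (1 − p0)^0.67. Example, p0 = 40%: p1 = 29.0%, D = 69.0, power = Φ(8.31 × 0.2002 − 1.960) = Φ(−0.297) = 38%.

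| Control risk (assumed) | Events from 200 | Power | Patients for 196 events |
|---|---|---|---|
| 20% | 34 | 21% | 1157 |
| 30% | 51 | 30% | 765 |
| 40% | 69 | 38% | 569 |
| 50% | 87 | 46% | 450 |
| 60% | 106 | 54% | 371 |

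**Step 3: proportion reading.** Here p1 = 0.67 × p0 and HR = ln(1 − p1) / ln(1 − p0).

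| Control risk (assumed) | Ketorolac risk | Implied HR | Power with 200 | Patients for 80% (Schoenfeld to Freedman) |
|---|---|---|---|---|
| 20% | 13.4% | 0.645 | 24.5% | 977 to 1012 |
| 30% | 20.1% | 0.629 | 37.5% | 587 to 607 |
| 40% | 26.8% | 0.611 | 52% | 390 to 405 |
| 50% | 33.5% | 0.589 | 68% | 269 to 283 |
| 58% | 38.9% | 0.567 | 80% | 203 to 213 |
| 60% | 40.2% | 0.561 | 82% | 190 to 200 |

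At 60% against 40.2%, a plain comparison of two proportions gives 198 patients. So 200 is a valid patient count on this reading if the control risk is about 58% to 60%.

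**Step 4: absolute reading.** A fall of 33 percentage points needs only about 22 to 77 patients over control risks of 35% to 90%, so it does not explain 200.

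**Step 5: what 200 patients can detect.** HR at 80% power = exp(−2 × 2.8016 / √D): 0.41 at 40 events, 0.49 at 60 and 0.57 at 100.

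**The case against.** The strongest defence is that section 4.5 is only a summary. It sends the reader to the protocol, where the control risk, event target and sidedness may be given, and a SAP may properly leave them there. It also speaks of recurrence, not of hazard. A relative fall of one third, from about 60% to 40%, is an ordinary reading of that and gives close to 200 patients. The population is described as high risk, DFS counts death from any cause, and two years is a minimum with visits out to five. The SAP therefore does not exclude a control risk near 60%.

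Most of this stands, and it rules out three stronger conclusions that a reader might draw:
- **That the 80% is certainly not delivered, or that no reading gives 200 patients.** Step 3 shows one that does.
- **That events were certainly mistaken for patients.** The match depends on choosing HR 0.67 and a two-sided test, neither of which is stated, and the proportion reading reaches 200 as well. The match suggests this error but does not prove it.
- **That the trial would miss the planned effect more often than not.** Power is below 50% only at control risks up to about 54% on the hazard reading, or about 38% on the proportion reading.

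The defence does not rescue the sentence as written. Section 4.5 restates the calculation as the basis for the patient number, and its listed assumptions do not give 200 patients unless an unstated and very high event risk is added.

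**Conclusion.** The point holds as a conditional one: the SAP states 80% power without the condition on which it depends. That condition is near-universal events if 33% means HR 0.67, or a control risk of about 58% to 60% (implied HR about 0.56 to 0.57) if it means a relative reduction in the cumulative proportion. Below that, the loss is large on either scale, as the two tables show.

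These figures assume a two-sided 5% test, proportional hazards, 1:1 allocation and no loss to follow-up. A one-sided test would soften them: on the proportion reading, 80% is then reached at a control risk of about 51.5%. Which control risk applies cannot be settled from the SAP.

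**What to change.** In section 4.5:

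1. Check the 200 against the protocol's calculation.
2. State whether the 33% is a hazard reduction or a relative reduction in the cumulative proportion, and whether the 5% is one- or two-sided.
3. State the assumed control DFS risk at the analysis and the required number of events on the chosen scale (196 to 202 if HR 0.67, two-sided).
4. Replace the unconditional 80% with the power, or the HR detectable with 80% power, for the events expected from 200 patients at cut-off.
5. Add that a non-significant result will be interpreted by the 95% confidence interval for the HR, and that an interval containing the planned effect does not exclude it.

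If the protocol supports a control risk near 60% on the proportion scale, the 80% can stay with that condition written beside it. The log-rank analysis does not change and no increase in sample size is needed. The cost is a few sentences and, possibly, a less favourable stated power.

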### 4.6 Randomization

This is a double blind study. Eligible patients will be randomized into the treatment arms with a ratio of 1:1 (ketorolac: placebo) as follows: Randomization will be performed 2 to 4h before surgery. A number will be assigned to each patient, as well as a treatment number, corresponding to ketorolac (30mg) or placebo (NaCl 0.9% 3 mL). Both are identical looking. In case of emergency, an unblinding envelope will be available. In both treatment groups, the randomized treatment will be administered by slow IV infusion at the induction of anesthesia.

The randomization will not be stratified.

# PERSONNEL

The statistical analysis of the study will be conducted by the statistical support unit of the King Albert II Institute.

# ANALYSIS POPULATIONS

In accordance with recommendations depicted in the ICH E9 guideline, the following analysis populations are defined as follows:

### 6.1 Full Analysis Set

The Full Analysis Set (FAS) population is defined as all subjects who have been randomized into the study, whether they actually received treatment or not. Subjects will be analyzed according to the treatment group to which they were randomized. This corresponds to the intent-to-treat (ITT) principle. The FAS population will be the set used for all the efficacy analyses, unless otherwise specified.

### 6.2 Per Protocol Set

The Per Protocol (PP) Set population will comprise all subjects who qualify for the FAS and who do not have any of the following major protocol deviations:

Violated the study entry criteria

Have taken banned concomitant medications (list available in Appendix II)

Did not receive treatment as per protocol (mis-randomized)

Potential protocol violators will be identified and reviewed to determine whether they will be excluded from the PPS population. This will take place in a review meeting prior to database lock. The above list is not an exclusive list of major violations. Other violations may be identified during the review. Formal sign-off of the final list of patients to be excluded from the Per Protocol analysis will take place after database lock. Every effort will be made to ensure that decisions will not be influenced by the treatment group to which the patient has been randomized. This analysis population will be used to support the primary efficacy analysis.

### 6.3 Safety Analysis Set

The Safety Analysis Set population will include all subjects who have taken at least one dose of study medication. Subjects will be analyzed according to the study medication they received. The safety population will be used for all safety analyses.

# GENERAL STATISTICAL METHODOLOGY

### 7.1 General Statistical Conventions

The following general statistical conventions will be implemented, unless the statistical analysis plan or protocol specify otherwise:

- For continuous variables, descriptive statistics will include the number of subjects (n), mean, standard deviation, minimum, median and maximum. For categorical data, frequency counts and percentages will be presented.
- Analysis of all efficacy and safety variables will be based on observed data
- Day converts to month: use number of days divided by 30.4
- Day converts to year: use number of days divided by 365.25
- If more than one measurement of a parameter is performed during the screening period, then the last of all such measurements prior to treatment will be considered the “baseline” value for that patient.
- All data processing, summarization and analyses will be performed using SAS®, Version 9.4 or later.

### 7.2 Covariates

No stratification factors will be considered in efficacy analyses as covariates.

### 7.3 Visit Windows

Tumor assessments will be followed at least every year, according to standard practice.

### 7.4 Missing Dates

#### 7.4.1 Recurrence Date

In the unlikely event that a patient’s date of recurrence is completely missing or partially missing, the date of progression will be treated as described in this section to estimate the time to events in the efficacy analyses:

- - If the month and year of recurrence are known (i.e. only the day is missing), the patient will be censored at the last documented scheduled tumor assessment closest to the month.
  - If only the year of recurrence is known (i.e. both the day and the month are missing), the patient will be censored at the last documented scheduled tumor assessment within the year or at the last documented scheduled visit in the previous year if there is no documented tumor assessment in the year.
  - If the date of recurrence is completely missing, the patient will be censored at the last documented scheduled tumor assessment

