#### 7.4.2 Death Date

In the unlikely event that a patient’s death date is missing, the date of death will be assumed as described in this section in calculating the time to events (DFS, LFS, MFS or OS) in the efficacy analyses:

- - If the information of date of death is partially or completely missing, the patient will be censored at the last documented information obtained for living patient.

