# EFFICACY VARIABLES

Events for LFS will mean CRF 20 OR 99 = Yes,

- Locoregional recurrence-free survival (LFS)

A patient’s locoregional survival time is defined as the time from surgery to the date of locoregional recurrence/death from any cause. In the case of patients who did not present a locoregional recurrence at the time of data-cut-off, the survival time will be censored.

| LFS (days) | = Date of locoregional  recurrence / Death/  Censoring | - Date of surgery + 1 |
| --- | --- | --- |
|  |  |  |

The censoring rules used in the calculation of LFS will be obtained from Table 1 below.

| **Table 1. Censoring rules used in the calculation of LFS** | | |
| --- | --- | --- |
| **Situation** | **End date** | **Censored** |
| Documented locoregional recurrence during the study | Date of the 1st assessment of the series of tests that determined locoregional recurrence | Noa |
| Death during the study before locoregional recurrence | Date of death | No |
| Locoregional recurrence documented between scheduled visits | Date of the 1st assessment of the series of tests that determined locoregional recurrence | No |
| Discontinued due to locoregional recurrence, but no documented locoregional recurrence. | Date of last tumor assessment before discontinuation. | Yes |
| No baseline assessments | Date of surgery | Yes |
| Death or locoregional recurrence after one or more missed scheduled assessments | Date of last tumor assessment | Yes |
| Patients still on treatment without PD as of data cut-off | Date of last tumor assessment | Yes |

a Earliest date among the dates used in calculating the progression-free survival.

- Disease-free survival (DFS)

A patient’s DFS is defined as the time from surgery to the date of disease recurrence/death from any cause. In the case of patients who did not present any event (i.e. those lost to FU or patients who did not have any recurrence at the time of data cut-off), DFS will be censored.

| DFS (days) | = Date of recurrence /  Death/ Censoring | – Date of surgery + 1 |
| --- | --- | --- |

The censoring rules used in the calculation of DFS will be obtained from Table 2 below.

| **Table 2. Censoring rules used in the calculation of DFS** | | |
| --- | --- | --- |
| **Situation** | **End date** | **Censored** |
| Documented recurrence during the study | Date of the 1st assessment of the series of tests that determined recurrence | Noa |
| Death during the study before recurrence | Date of death | No |

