| Recurrence documented between scheduled visits | Date of the 1st assessment of the series of tests that determined recurrence | No |
| Discontinued due to recurrence, but no documented recurrence. | Date of last tumor assessment before discontinuation. | Yes |
| No baseline assessments | Date of surgery | Yes |
| Death or recurrence after one or more missed scheduled assessments | Date of last tumor assessment | Yes |
| Patients without recurrence as of data cut-off | Date of last tumor assessment | Yes |

a Earliest date among the dates used in calculating the progression-free survival.

How can this be found ? Using CRF 20, 30 OR 99 = Yes.

- Metastasis-free Survival (MFS)

A patient’s MFS is defined as the time from surgery to the date of metastasis occurence/death from any cause. In the case of patients who did not present an event (i.e. those lost to FU or patients who did not have any metastases at the time of data-cut-off), MFS will be censored.

| MFS (days) | = Date of metastasis /  Death/ Censoring | – Date of surgery + 1 |
| --- | --- | --- |

The censoring rules used in the calculation MFS will be obtained from Table 3 below.

| **Table 3. Censoring rules used in the calculation of MFS** | | |
| --- | --- | --- |
| **Situation** | **End date** | **Censored** |
| Documented metastases during the study | Date of the 1st assessment of the series of tests that determined metastases | Noa |
| Death during the study before metastases | Date of death | No |
| Metastases documented between scheduled visits | Date of the 1st assessment of the series of tests that determined metastases | No |
| Discontinued due to metastases, but no documented recurrence. | Date of last tumor assessment before discontinuation. | Yes |
| No baseline assessments | Date of surgery | Yes |
| Death or metastases after one or more missed scheduled assessments | Date of last tumor assessment | Yes |
| Patients without metastases as of data cut-off | Date of last tumor assessment | Yes |

a Earliest date among the dates used in calculating the progression-free survival.

How can this be found ? Using CRF30, 99 = Yes.

- Overall Survival (OS) (event: CRF 99 = Yes)

A patient’s survival time will be defined as the time from surgery to the date of death due to any cause. If the patient has not died, the survival time will be censored on the last date the patient was known to be alive.

| Overall Survival (days) | = Date of death / censoring | - Date of surgery + 1 |

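### SAP 7.4.1 and 7.4.2 censor patients known to have recurred or died when the date is incomplete, contrary to the SAP's own endpoint definitions

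*SAP*

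**What the plan says.** **Recurrence (SAP 7.4.1).** Three cases of a known recurrence with an incomplete date all end in censoring.

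- Day missing: "If the month and year of recurrence are known (i.e. only the day is missing), the patient will be censored at the last documented" planned assessment nearest that month.
- Day and month missing: "the patient will be censored at the last documented scheduled tumor assessment within the year", or at the last scheduled visit of the year before if that year has no assessment.
- Nothing known: "If the date of recurrence is completely missing, the patient will be censored at the last documented scheduled tumor assessment".

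**Death (SAP 7.4.2).** The lead-in says a date of death will be assumed "in calculating the time to events (DFS, LFS, MFS or OS) in the efficacy analyses". The only rule that follows assumes no date: "If the information of date of death is partially or completely missing, the patient will be censored" at the last information showing the patient alive.

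**Definitions (SAP, Efficacy Variables).** "A patient’s DFS is defined as the time from surgery to the date of disease recurrence/death from any cause". DFS censoring is introduced with "In the case of patients who did not present any event". Tables 1 to 3 list a documented event, and a death before it, as not censored. The DFS event flag is a yes on CRF 20, 30 or 99, with no condition on the date. For OS: "If the patient has not died, the survival time will be censored on the last date the patient was known to be alive".

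**Adverse events (SAP, Safety Variables).** A partial start date is imputed, to the first of the month or to 1 January.

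**The concern.** In all these cases it is known that the event happened; only the timing is uncertain, sometimes by no more than days within a month. The SAP responds by removing the event. Three problems follow.

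- **Contradiction.** A programmer working from the Efficacy Variables section codes an event. One working from 7.4 codes a censored observation. The primary endpoint is affected.
- **Informative censoring.** These patients are censored because they had the event. Kaplan-Meier and log-rank methods assume that censoring carries no such information.
- **Credit for time after the event.** In 7.4.1 the censoring date can fall after the recurrence, because it may be the nearest assessment, the last one in the year or the last one on file. As an illustration, for a relapse in March recorded only by year and an assessment in November, the patient is counted as event-free for about eight months after relapse.

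**Working it through.** **1. Text comparison**

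| Known fact | Efficacy Variables section | Section 7.4 |
| --- | --- | --- |
| Recurrence, date incomplete | Event for DFS, and for LFS or MFS by type | Censored |
| Death, date incomplete | Event for OS; event for DFS, LFS and MFS if it comes first | Censored |
| Patient has died (OS) | Only patients who have not died are censored | Censored if any part of the date is missing |

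**2. Reach.** The recurrence rule touches DFS, LFS and MFS, not OS. The death rule touches OS. It removes a DFS, LFS or MFS event only when no dated event for that endpoint came earlier.

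**3. The plan's own figure.** SAP 4.5 gives 200 patients for a 33% reduction in recurrence, 5% type I error and 80% power, but no control event rate, so a patient number cannot be derived from its inputs. For HR 0.67, two-sided, the required events are 4 × (1.960 + 0.842)² / (ln 0.67)² = 196 (Schoenfeld); Freedman's formula gives 202. The point here does not depend on this figure. The 196 events are used below only as a reference with 80% power.

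**4. Power.** Let f be the share of events with incomplete dates (assumed; the SAP gives none). Power = Φ(½ × √(d(1 − f)) × |ln 0.67| − 1.96), where d is the number of events. The second row assumes 60 events, that is 30% of 200 patients.

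| d | f = 0 | 5% | 10% | 20% |
| --- | --- | --- | --- | --- |
| 196 | 80.0% | 78.0% | 75.8% | 70.8% |
| 60 | 34.1% | 32.7% | 31.3% | 28.3% |

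The loss is about 2 to 9 points at 196 events and about 1 to 6 points at 60.

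**5. Kaplan-Meier bias.** Assume a true 2-year DFS of 70%, a constant hazard, and affected patients censored at the preceding yearly visit (simulation of 400,000 patients).

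| f | Estimated 2-year DFS | Overstatement |
| --- | --- | --- |
| 0 | 70.0% | none |
| 5% | 71.2% | 1.2 points |
| 10% | 72.3% | 2.3 points |
| 20% | 74.9% | 4.9 points |

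A rough check is 0.70^(1 − f), which applies if censoring falls at the event time itself: 71.3%, 72.5% and 75.2%. Censoring after the recurrence would push the curve higher still, so the table is not the worst case.

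**6. Hazard ratio.** To a first approximation, apparent HR = true HR × (1 − f in ketorolac) / (1 − f in placebo). Equal f cancels. With 10% in one arm and 0% in the other, a true HR of 1.00 appears as 0.90 / 1 = 0.90 or 1 / 0.90 = 1.11.

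**7. Cost of imputing.** With the month known and day 15 used, the largest error is 31 − 15 = 16 days, and 16 / 730 is about 2% of two years.

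**The case against.** The strongest reply is that this will hardly ever happen. Both sections call an incomplete date unlikely, and Tables 1 to 3 date an event by the first assessment in the series of tests that established it. If that assessment is fully dated, 7.4.1 may never be reached. With zero or one such case the numerical effect is negligible. This stands as a limit on size. It does not remove the contradiction, which exists at any frequency.

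A second reply is that the SAP elsewhere censors known events on purpose: Tables 1 to 3 censor a death or recurrence that follows a missed assessment. That is true for DFS, LFS and MFS, but those rows deal with gaps in follow-up, not with incomplete dates. OS has no such table.

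A third concerns the comparison. The trial is double-blind and 1:1, so there is no evident reason for incomplete dates to differ by arm. This also stands. A reader might infer that the rule tilts the log-rank test towards one arm, and the document does not support that. Unequal loss is possible, not shown.

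Two further inferences should be resisted. One is that OS suffers proportionally more because deaths are fewer. With the same share of incomplete dates the proportional loss is the same, and nothing shows that death dates are less complete than recurrence dates. The other is that every incompletely dated death removes an event from all four endpoints; step 2 of the working shows that it does not.

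Finally, imputation is easier to defend when the month is known than when only the year, or nothing, is known. That is correct and shapes the fix.

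**Conclusion.** The point holds as a matter of text. Sections 7.4.1 and 7.4.2 recode known recurrences and deaths as censored. This contradicts the endpoint definitions and the promise in 7.4.2 to assume a date, and it differs from the imputation used for adverse events. The direction is clear: curves too high and events lost. The hazard ratio is roughly unbiased under equal loss and biased otherwise.

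The size is unknown, because the SAP states neither the frequency of incomplete dates nor an expected event rate. The figures of about 1 to 5 points on 2-year DFS and about 1 to 6 points of power rest on an assumed 5 to 20% of events affected, a true 2-year DFS of 70% and 60 events. If incomplete dates prove as rare as the SAP expects, the effect will be smaller. The rule should still be corrected before unblinding, since it leaves the coding of the primary endpoint open to two readings.

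**What to change.** Replace the rules in 7.4.1 and 7.4.2 so that a known recurrence or death counts as an event, with its date imputed as follows.

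- **Month and year known:** day 15, moved where necessary so that it lies between the last event-free assessment (for death, the last date known alive) and the first record of the event.
- **Only the year known:** the midpoint of the part of that calendar year lying between the last event-free contact and the first record of the event. The restriction to the recorded year matters. With visits at 2 and 5 years, an unrestricted midpoint falls at 3.5 years, which can lie outside that year.
- **Nothing known:** the midpoint between the last event-free contact and the first record of the event.

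Keep the present censoring as a sensitivity analysis, and report the number of imputed dates by arm so that any imbalance can be seen. The rows in Tables 1 to 3 on missed assessments are a separate matter and need not change for this.

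The cost is a few lines of SAP text and code. The downside is error in the imputed dates: at most about 16 days when the month is known, and up to half the bounding interval for the midpoint rules. That can be long where contacts are sparse.
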